## Results

This clinical trial began enrollment in April 2018. As of publication, 40 subjects have been evaluated, 25 have been included satisfactorily, and 10 participants have completed the entire protocol. We estimate enrollment will be completed within 2 years. Results will be presented at scientific meetings and published in peer-reviewed journals. All publications will be authorized by the study investigators.

## Discussion

This study will assess a relevant public health problem, as the overall population is getting older and the prevalence of chronic disorders is increasing. This randomized clinical trial will evaluate the effects of the cumulative noninvasive brain stimulation technique as an instrument to decrease pain intensity by inducing neuroplasticity in brain circuits related to central sensitization. As a secondary effect, we will observe impact on the quality of life and mobility performance in elderly patients with knee OA.

This trial will contribute to understanding the underlying mechanisms of the analgesic effects of tDCS over the motor cortex by assessing the CPM response of the subjects. In this trial, we are only enrolling subjects with defective endogenous inhibitory pain system. We chose this criteria given the mechanisms of tDCS, as well as effects of tDCS on this system [57-58]. Therefore, this study will be important to preliminarily test the suitability of CPM as a valuable prognostic and surrogate marker. Finding better neurophysiological markers for the use of tDCS is critical to advance this field. A potential significant correlation between pain scores and CPM response will indicate that CPM may be a useful marker.

Most interventions for OA do not target the central sensitization and defective descending inhibitory pain system. For instance, nonsteroidal anti-inflammatory drugs inhibit the two recognized forms of prostaglandin synthase, thus providing an analgesic and anti-inflammatory effect; however, their prolonged use is limited because they carry risk for cardiovascular and upper gastrointestinal diseases [59,60]. Thus, tDCS can be important for nonresponders to the traditional treatment. This intervention has the opposite effect on the endogenous pain system when compared to opioids, which, when used chronically, may increase sensitivity to a noxious stimulus and consequently induce hyperalgesia [61].

Another important finding from this trial concerns the additional data we will provide on the tDCS effects in elderly populations. While there have been a fair number of trials testing tDCS in chronic pain, there have been few randomized clinical trials testing tDCS for chronic pain in elderly patients. To date, there have been no well-powered trials (such as this one with 104 subjects) designed to test a homogenous population [29,62,63]. We believe that this trial can provide important information to advance this therapy in this population.

We decided to use 15 stimulation sessions based on a recent trial on chronic pain due to fibromyalgia, which estimated 15 tDCS sessions as the median number of stimulations to produce clinically meaningful outcomes [37].

The safety of tDCS has been well established, and after several studies, researchers concluded that tDCS induces only temporary mild effects. The most common side effects include headache, dizziness, nausea, mild pain, itchy sensation, and skin redness under area of the electrodes [26,38,55-57]. However, it is important to assess safety in elderly patients given that there is much less experience with this population. This trial will provide additional data for this domain, which will be useful when planning future trials.

Some concerns about the study should be discussed. One of the possible issues may be the combination with other therapies, which may influence the results. Given the relatively large sample size of subjects, we believe that this potential covariate will be balanced in the two groups. In addition, subjects will be asked to remain stable in their drug treatment, and any changes will be noted for secondary subgroup analysis. Finally, although blinding is not perfect in tDCS and 10% to 20% may become unblinded, we have demonstrated in longitudinal trials that there are no blinding-related biases in a tDCS clinical trial for a parallel design [64]. This trial has several strengths, such as a relatively large sample (one of the largest in tDCS pain research) and a population selected based on the endogenous mechanisms of tDCS (CPM).

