### Participants

Individuals aged 60 years and older, which is the definition for the elderly in Brazil [40], with an established diagnosis of unilateral or bilateral knee OA as established by the American College of Rheumatology criteria of 1986, using history, physical examination, and radiographic findings according to the Kellgren-Lawrence radiographic grading, will be recruited [41]. Patients will be recruited from HSP and from all the outpatient clinics belonging to the Federal University of São Paulo. Eligible subjects will have had pain in the knee for a minimum of 6 months, with an average pain score of 4 or more on a 0-10 numeric rating scale (NRS) for pain over that period and during the week prior to the first stimulation session. Following this, the subjects will be required to report a reduction on NRS during the CPM task of less than 10% compared to the pain score before the test.

Exclusion criteria include patients who have any severe acute or chronic uncompensated disease (such as uncontrolled hypertension, diabetes, cardiac issues, heart failure, or chronic obstructive pulmonary disease), history of epilepsy or syncope, contraindications to transcranial brain stimulation (ie, implanted brain medical devices or implanted brain metallic devices), established cognitive impairment, history of fractures in the lower limbs and/or spine in the last 6 months, traumatic brain injury with residual neurological deficits, alcohol abuse within the last 6 months as self-reported, use of carbamazepine within the last 6 months as self-reported, or severe depression (with a score of more than 30 on the Beck Depression Inventory). The principal investigator will obtain informed consent prior to enrolling participants in the study. We expect in this elderly population to have a female-to-male ratio of about 70%:30%.

In order to avoid drop outs, the principal investigator will follow up with all participants by phone during the entire study to remind them of the schedule. Participants and treating physicians will be told that changes in treatment during the study are strongly discouraged and must be reported. In addition, no treatment crossover will be permitted.

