#### Conditioned Pain Modulation

CPM will be measured using cold water as the conditioned stimulus and pressure as the test stimulus to assess endogenous pain modulation. Pressure will be applied using the same device and technique as for the PPT. Participants will be asked to immerse their contralateral hand to the most affected knee in a cold water bath maintained at 10^o^C for approximately 1 minute. In the last 30 seconds, the test stimulus will be applied following the PPT procedure [15-17].

We will calculate the percentage change in pain scores following CPM, a measurement we will call CPM-P, and the change in the PPT after the CPM that we will call CPM-PPT. Both of them will be calculated using the following formula: (post-CPM trial score − pre-CPM trial score / pre-CPM trial score) × 100. For CPM-P, a negative score will indicate pain inhibition after the conditioning stimulus. For CPM-PPT, a positive score will indicate pain inhibition after the conditioning stimulus.

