### Sample Size and Data Analysis

The sample size was estimated using the minimal clinically important difference (20% reduction from the baseline) in the outcome of pain intensity measured by the NRS as a parameter. The effect size and the probability of error type I (alpha) and type II (beta) were 0.59, .05, and .2, respectively. According to the sample calculation, that total size would be 94 participants. We will increase the sample size by 10% to account for dropouts and other unexpected factors. Thus, the final sample size is 104 subjects.

All analyses will be conducted according to the principle of intention-to-treat (ITT) using a regression-based single imputation method. The ITT population will include all randomized subjects. We will perform an additional sensitivity analysis in which we will use the method of multiple imputation. Initially, the baseline characteristics between sham and tDCS groups will be tested using Student *t* tests; to analyze our primary outcome, which is pain intensity measured by BPI, we will adopt a mixed analysis of variance model in which the dependent variable will be the outcome (BPI) and the independent variables will be group (tDCS-a or tDCS-s), time (baseline and after treatment and follow-up), and the interaction group time. Secondary analyses will be conducted in an exploratory manner (no correction for multiple comparisons). Similar analysis will be conducted for the adverse effects measuring continuous outcomes, and for the categorical outcomes, we will use Fisher exact tests. In both cases, for the safety analysis, we will use uncorrected *P* values to increase the likelihood of detecting detrimental adverse effects.

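### A significant pain–CPM correlation cannot test CPM as a surrogate marker, and enrolling only low-CPM patients limits the prognostic reading (minor)

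*Protocol article*

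**What the plan says.** Three statements stand close together in the Discussion. On selection: "we are only enrolling subjects with defective endogenous inhibitory pain system". The article then draws an aim from this: "Therefore, this study will be important to preliminarily test the suitability of CPM as a valuable prognostic and surrogate marker". It next says how a result would be read: "A potential significant correlation between pain scores and CPM response will indicate that CPM may be a useful marker".

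The Participants section makes the selection concrete. Each subject must show a fall in numeric pain rating of less than 10% during the CPM task. The Conditioned Pain Modulation section defines two CPM outcomes: CPM-P (percentage change in pain score) and CPM-PPT (change in pressure pain threshold). Sample Size and Data Analysis describes no marker analysis and calls secondary analyses exploratory and uncorrected.

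**The concern.** The article names two marker roles and offers one piece of evidence for both, which fits neither well.

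- **Surrogate.** This role requires that the treatment effect on CPM account for the treatment effect on pain. A pain–CPM correlation can exist without any treatment effect on CPM.
- **Prognostic.** This role is best shown across a range of CPM values. Enrolling only patients with reduced CPM removes the low-versus-normal contrast, so the aim does not follow from the selection in the way that the word *therefore* suggests.

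The article also does not say whether the correlation would be taken across both arms. If it were, treatment effects on the two variables would by themselves create some correlation. At stake is a mechanistic conclusion: CPM could be reported as a promising surrogate on evidence that does not bear on surrogacy, or a weak baseline correlation could be read as showing that CPM has no prognostic value.

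**Working it through.** **Inputs from the article (Sample Size and Data Analysis):** effect size 0.59, alpha 0.05 (two-sided assumed), beta 0.2, 94 participants, 104 after a 10% increase. Allocation is 1:1 (Randomization and Blinding).

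**Assumed, not in the article:** a within-arm pain–CPM correlation of 0.3 or 0.4; an unselected correlation of 0.30; and a normally distributed CPM reduction with mean 0–10% and SD 20%. The Introduction gives a reduction below 10% for elderly people with severe osteoarthritis pain, which motivates the range for the mean.

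**The plan's own figure.** A two-sided t-test at d = 0.59 with 80% power needs 46.08 per arm, so 47 per arm and 94 in total. Then 94 × 1.10 = 103.4, so 104. Both figures reproduce. No figure is given for the correlation.

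**How large a significant correlation must be.** The threshold is r = t/√(N − 2 + t²), with t the 97.5% point on N − 2 degrees of freedom.
- N = 94: |r| ≥ 0.203, which is 4.1% shared variance.
- N = 104: |r| ≥ 0.193, which is 3.7% shared variance.

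**Does significance imply that CPM carries the effect?** Simulate a pain effect of 0.59 SD, no treatment effect on CPM, and within-arm correlation ρ. The expected correlation across arms is ρ/√(1 + 0.59²/4) = ρ/√1.087, that is 0.288 for ρ = 0.3 and 0.384 for ρ = 0.4. Share of trials with a significant correlation:

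| N | ρ = 0.3 | ρ = 0.4 |
|---|---|---|
| 94 | 81% | 97% |
| 104 | 85% | 98% |

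The criterion is usually met although CPM explains none of the treatment effect. Taking the correlation within arm does not cure this, because the within-arm correlation is real. It is simply not evidence of surrogacy.

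**What pooling alone adds.** With zero within-arm correlation and treatment effects d₁ on pain and d₂ on CPM, the pooled r = (d₁d₂/4)/√[(1 + d₁²/4)(1 + d₂²/4)].
- 0.59 and 0.59: 0.0870/1.0870 = 0.08. Fisher z at N = 104: 0.0803 × √101 = 0.81, so about 13% of trials are significant.
- 0.59 and 1.0: r = 0.13, about 25%.
- 0.8 and 0.8: r = 0.14, about 29%.
- 1.0 and 1.0: r = 0.20, about 53%.

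**What selection does to a correlation with baseline CPM-P.** Put c = (10 − mean)/20 and λ = φ(c)/Φ(c). The SD ratio is u = √(1 − cλ − λ²), and the restricted correlation is r′ = ru/√(1 − r² + r²u²).
- Mean 0%: c = 0.5, λ = 0.509, u = 0.70, r′ = 0.21.
- Mean 10%: c = 0, λ = 0.798, u = 0.60, r′ = 0.19.

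Power at N = 104 falls from about 87% for r = 0.30 to 59% and 47% respectively. As a rough cross-check, the Results section reports 25 of 40 evaluated subjects included (62.5%). If selection on CPM kept the lowest 62.5%, 0.30 would fall to 0.20. Other eligibility criteria also act on that share.

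**The case against.** The best defence is that the text is cautious and is not an analysis plan. The marker sentence says only that CPM *may* be useful, the test is called preliminary, and the words prognostic and surrogate stand in a separate sentence. CPM as a marker is not in the stated objective or aim, where CPM is a secondary outcome. This stands, and it keeps the point minor. It does not remove it: the correlation is the only evidence the article offers for the marker aim, and a correlation is not even preliminary evidence of surrogacy.

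Some stronger readings are tempting, and the article does not support them:

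- **That a correlation would be taken as proof of a surrogate.** The hedged wording does not say so.
- **That the arms will be pooled.** The article does not say this, so the pooling result is conditional. At the trial's own planning effect on both variables it is about 13%; the rates of 29% to 53% need 0.8 to 1.0 SD on both.
- **That selection weakens every pain–CPM correlation.** Selection acts on baseline CPM-P. It does not directly truncate post-treatment CPM, CPM change or CPM-PPT.
- **That the mean CPM reduction might be 17%.** The Introduction gives that value for healthy elderly people, not for this population.
- **That the article claims marker value outside patients with reduced CPM.** It makes no such explicit claim. An association within the enrolled range is a legitimate exploratory look.

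**Conclusion.** The point holds as a minor one. A significant pain–CPM correlation does not test surrogacy: with the planning effect on pain, none on CPM, and an assumed within-arm correlation of 0.3–0.4, it appears in about 80% to 98% of trials of 94 to 104 patients. If arms are pooled, parallel treatment effects add a false-positive route, about 13% at 0.59 SD on both and more if the effects are larger. Selection removes the normal-CPM contrast and weakens correlations with baseline CPM-P, from 0.30 to about 0.19–0.21. That last figure rests on the assumed mean, SD, normal shape and true correlation.

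A reader might infer that the trial's main result is at risk. It is not: the primary outcome, its model, the sample size and the safety analyses do not depend on this passage.

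**What to change.** Replace the marker sentence in the Discussion so that it states the following:

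1. The pain–CPM association will be estimated within arm, or adjusted for arm and baseline values, with a confidence interval. It will be labelled exploratory and hypothesis-generating.
2. The word *surrogate* is dropped, or is limited to an exploratory report of how far the arm effect on BPI pain changes after adjustment for CPM change. That report should say that it does not establish surrogacy: CPM change is not randomised, and one trial of about 100 patients cannot settle the question.
3. Any prognostic reading holds only within patients with reduced CPM.

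The cost is a little extra analysis of data already being collected, and a narrower claim.

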## Abbreviations

BPI: Brief Pain Inventory
CPM: conditioned pain modulation
CPM-P: percentage change in pain score following conditioned pain modulation
CPM-PPT: change in pressure pain threshold after conditioned pain modulation
CONSORT: Consolidated Standards of Reporting Trials
HSP: Sao Paulo Hospital
ITT: intention-to-treat
M1: primary motor cortex
MDT: mechanical detection threshold
MPT: mechanical pain threshold
NRS: numeric rating scale
OA: osteoarthritis
PPT: pressure pain threshold
tDCS: transcranial direct current stimulation
tDCS-a: active transcranial direct current stimulation
tDCS-s: sham transcranial direct current stimulation
VAS: visual analog scale
VFM: Von Frey monofilament
